### Randomisation

Patients have to sign an informed consent for the involving in the trial a day before endoscopic procedure. Randomisation will be performed at the time of transfer to the endoscope room by using random number generator at http://www.stattrek.com.

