### Study design

After diagnosis, patients with obstructive jaundice will be divided into two groups: (A) the test group in which will be administered UDCA in the early phase after endoscopic treatment, and (B) control group, in which no treatment will be applied with UDCA.

Diagnostic methods will be biochemical findings, ultrasound examination, endoscopic retrograde cholangio pancreatography (ERCP), CT-scan and magnetic resonance cholangio pancreatography (MRCP).

Serum-testing in patients with obstructive jaundice will include determination of bilirubin (total and direct fractions), alanine transaminase (ALT), aspartate transaminase (AST), gama-glutamil transpeptidase (GGT), alkaline phosphatase, albumin, and cholesterol levels. These parameters will be determined one day prior endoscopic intervention, and on the third, fifth, seventh, tenth, twelfth and fourteenth days after endoscopic intervention.

Endoscope procedure that will end with the internal derivation of bile shall be named as the internal bile drainage.

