### UDCA administration

UDCA administration will begin twenty-four hours after endoscopic procedure and will last fourteen days. UDCA dose will be administered at 750 mg/day, divided into three doses.

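### The random draw is made before the endoscopic procedure although UDCA starts 24 hours after it, so failed procedures and early complications are already in the arms when treatment begins

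*Protocol article*

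**What the plan says.** Three sections of the protocol article fix the sequence.

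- **Randomisation:** "Patients have to sign an informed consent for the involving in the trial a day before endoscopic procedure", and then "Randomisation will be performed at the time of transfer to the endoscope room by using random number generator". Allocation therefore precedes the procedure.
- **UDCA administration:** "UDCA administration will begin twenty-four hours after endoscopic procedure and will last fourteen days".
- **Study design:** "After diagnosis, patients with obstructive jaundice will be divided into two groups", with UDCA in one group and none in the other. The same section says: "Diagnostic methods will be biochemical findings, ultrasound examination, endoscopic retrograde cholangio pancreatography (ERCP", followed by CT and MRCP. It also gives a name to successful drainage: "Endoscope procedure that will end with the internal derivation of bile shall be named as the internal bile drainage".

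The general aim and the study objectives place the question in the early period after the endoscopic intervention, and the objectives describe the trial as open-label. The inclusion criteria do not mention drainage. Cholangitis and acute pancreatitis are exclusion criteria without a stated time point. The only exclusion described during the trial is for serious side effects or allergic reactions after UDCA.

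**The concern.** By design the arms do not differ until a day after the procedure, yet allocation is settled before it. Two kinds of event can occur in between: the procedure may fail to relieve the obstruction, or the patient may develop acute pancreatitis or cholangitis, both of which the trial excludes. Such patients are not in the state that the trial set out to study, but they are already in an arm.

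Three consequences are possible.

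1. If they stay in the analysis and cannot benefit from UDCA, the difference between arms shrinks.
2. If they are removed by someone who knows the arm, removal may differ between arms.
3. If the endoscopist knows the arm, the procedure itself could be carried out differently in the two groups. Analysing everyone would not repair this, because it concerns care given and not who is counted.

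Nothing in the article shows a need for the early draw. Consent is already in hand the day before, and the result of the draw is not used until a day after the procedure.

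**Working it through.** **Order of events, from the three sections above**

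| Time | Event |
|---|---|
| Day before procedure | Consent; baseline blood tests |
| Transfer to endoscopy room | Randomisation |
| Then | Endoscopic procedure, outcome not yet known at allocation |
| 24 hours after procedure | First UDCA dose in the test group |

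The interval between allocation and first dose thus contains the whole procedure plus 24 hours.

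**Inputs** (Power of the study): improvement 70% versus 40%, alpha 0.05, power 80%, at least 48 per group. Two-sided testing is assumed, as the article does not state it. The statistical section names the chi-square and Fisher exact tests for proportions.

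**Step 1: reproduce 48 per group.** With a mean proportion of 0.55:

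n = [1.960 × √(2 × 0.55 × 0.45) + 0.8416 × √(0.70 × 0.30 + 0.40 × 0.60)]² / 0.30² = (1.379 + 0.565)² / 0.09 ≈ 42.0

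With continuity correction: n′ = (n/4) × [1 + √(1 + 4/(n × 0.30))]² = 10.49 × (1 + 1.148)² ≈ 48.4. This is 48 to the nearest whole number, or 49 rounded up. Exact power of the two-sided Fisher test at 48 per group is 0.800. The plan's figure is therefore reproduced, and on the Fisher test it holds no reserve.

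**Step 2: dilution.** The article gives no rate of failed procedures or early complications. Assume a share f of each arm that stays in the analysis and responds at the 40% control rate in both arms. Then

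- UDCA arm: 0.70 × (1 − f) + 0.40 × f = 0.70 − 0.30f
- Control arm: 0.40
- Difference: 0.30 × (1 − f)

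Exact power is the sum, over all pairs of responder counts out of 48 and 48, of the product of the two binomial probabilities wherever the test is significant.

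| Assumed f | UDCA arm | Difference (points) | Power, Fisher | Power, uncorrected chi-square |
|---|---|---|---|---|
| 0% | 70.0% | 30.0 | 0.800 | 0.854 |
| 5% | 68.5% | 28.5 | 0.754 | 0.815 |
| 10% | 67.0% | 27.0 | 0.702 | 0.770 |
| 15% | 65.5% | 25.5 | 0.646 | 0.721 |

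**Step 3: cost in patients.** Using the continuity-corrected formula of step 1, rounded up, 80% power would need 54, 60 or 67 per group at f = 5%, 10% or 15%, against 49 without dilution.

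**Step 4: the two statements on allocation time.** Study design places allocation after diagnosis; Randomisation places it at transfer. The two agree if the diagnosis comes from biochemistry, ultrasound, CT or MRCP. They disagree only if ERCP must be finished before the diagnosis counts as made. Study design lists ERCP as a diagnostic method but does not set that order, so the text is ambiguous.

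**The case against.** The strongest reply is that randomising before the procedure is valid. If every randomised patient is analysed, the comparison is unbiased and the only cost is some dilution. That stands.

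Four stronger readings are tempting, and the document does not support them.

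- **That the article contradicts itself on allocation time.** Entry needs obstructive jaundice and bilirubin above 50 μmol/l, which can be established before transfer. Consent the day before presupposes a working diagnosis. This is an ambiguity.
- **That patients will be dropped after allocation.** No section says so. The exclusion criteria read most naturally as entry criteria, and the handling of such patients in the analysis may be in a full protocol or SAP that is not shown. Selection bias is therefore conditional on a step that the article does not describe.
- **That the endoscopist will know the arm and act on it.** Open-label does not mean that the endoscopist is told, and no section describes a drainage decision that could depend on the arm. It is a possibility that a later draw would remove.
- **That the power loss is established.** The shares are assumed. The model gives affected patients no benefit at all, although a drained patient with a complication might still benefit. It also takes the 70% and 40% as describing only patients free of these events. If those rates already describe everyone randomised, the dilution is already counted. At 5%, chi-square power is still above 80%.

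What remains is that the article itself fixes the time of the draw, and an analysis plan cannot move it. The early draw carries these risks for no stated gain.

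**Conclusion.** The point holds as a weakness of design. Allocation precedes the event that defines the population of interest, and the treatment contrast begins only 24 hours after that event. The consequence to expect is dilution, of unknown size. Under assumed shares of 5% to 15% with no UDCA benefit, and with the planned rates taken to describe unaffected patients, power at 48 per arm falls to between 75% and 65% by the Fisher test, or between 82% and 72% by uncorrected chi-square. Bias is a conditional risk: it needs either removal of patients after allocation or knowledge of the arm during the procedure. Because a valid analysis of all randomised patients remains possible and no event rate is given, this is something the sponsor should fix; it is not a fault that defeats the trial.

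**What to change.** Keep consent on the day before. Make the random draw after the endoscopic procedure, immediately before UDCA would start, in patients who at that point still meet the inclusion criteria as assessed at entry and none of the exclusion criteria. The words *as assessed at entry* matter for bilirubin, which may fall once bile drains. Whether completed internal drainage is a condition for randomisation is for the sponsor to decide and state; the present criteria do not require it, and adding it would narrow the population.

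In Study design, say what is meant by allocation after diagnosis and whether ERCP belongs to that diagnosis, so that the section agrees with Randomisation.

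Cost: the draw moves by about a day, and a few consented patients are not randomised, so slightly more must be approached to reach 48 per group. The sample size itself does not change.

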### Specific aims

Specific aims are:

– To evaluate the effect of UDCA in relation to the aetiology of obstructive jaundice.

– To assess that in which functional parameters of the liver, treatment with UDCA will have greater impact.

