## Methods/Design

### Study objectives

This trial will be a prospective, open-label, randomized, and controlled study. The objective will be to evaluate the effect of ursodeoxycholic acid (UDCA) in the functional restoration of the liver in patients with obstructive jaundice in the early post-endoscopic phase.

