### Power of the study

A clinically relevant improvement of liver functional tests is defined as an improvement of 70% of liver functional tests in test group, and an improvement only 40% in control group. In our study, to have an 80% chance of detecting about a 40% difference (70% vs. 40%) between two groups on improvement of liver functional tests at an alpha level of 0.05, the power calculation indicates that each of the two groups should have at least 48 patients.

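### The on-demand web draw has no stated safeguard against redrawing, and neither it nor the stated tests take account of aetiology, the subject of the first specific aim

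*Protocol article*

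**What the plan says.** The Randomisation section of the protocol article has two sentences. The first is on consent: "Patients have to sign an informed consent for the involving in the trial a day before endoscopic procedure". The second gives the time and the tool: "Randomisation will be performed at the time of transfer to the endoscope room", "by using random number generator" on a public website. No allocation ratio, list, block scheme, stratum, operator or record of the draw is mentioned.

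Other sections that bear on this:

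- **Study objectives:** "This trial will be a prospective, open-label, randomized, and controlled study".
- **Study design:** the comparator is "B) control group, in which no treatment will be applied with UDCA". This section places the division into groups after diagnosis and counts ERCP among the diagnostic methods.
- **UDCA administration:** treatment starts 24 hours after the procedure, so allocation is fixed at least a day earlier.
- **Specific aims:** the first is "To evaluate the effect of UDCA in relation to the aetiology of obstructive jaundice".
- **Power of the study:** "each of the two groups should have at least 48 patients".
- **Data collection and statistical analyses:** chi-square or Fisher tests for proportions, and t, Mann-Whitney, ANOVA or Kruskal-Wallis tests for quantitative variables. None is said to adjust for aetiology.

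**The concern.** A random number taken from a public page at the moment of need can be taken again. In an open-label trial with no placebo, the number shows the arm at once. Allocation would be exposed to redrawing or overriding unless someone independent makes the draw or it is recorded beyond alteration, and the article names neither safeguard.

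The second issue is aetiology. The Background lists causes from bile duct stones to pancreatic carcinoma, and the trial wants to know whether the UDCA effect depends on the cause. A simple draw balances causes between arms only on average, and the stated tests do not correct for the imbalance that occurs. The aim is therefore protected neither by the design nor by the stated analysis.

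**Working it through.** **1. The plan's own figure.** Inputs from Power of the study: rates 0.70 and 0.40, alpha 0.05 (two-sided assumed, as sidedness is not stated), power 80%.

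- Pooled-variance formula: n = [1.960·√(2·0.55·0.45) + 0.8416·√(0.21 + 0.24)]² / 0.30² = (1.379 + 0.565)² / 0.09 = 41.97, so 42 per arm.
- Continuity correction: (n/4)·[1 + √(1 + 4/(0.30·n))]² with n = 41.97 gives 48.4, which is 49 rounded up and 48 rounded to the nearest patient.

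The stated 48 per arm is therefore reproduced. The total of 2 × 48 = 96 is used below.

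**2. Arm sizes under a simple 1:1 draw of 96.** The size of one arm is Binomial(96, 0.5).

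| Event | Probability |
|---|---|
| Exactly 48/48 | 8.1% |
| Smaller arm 43 or fewer | 35.8% |
| Smaller arm 40 or fewer | 12.5% |
| Smaller arm 38 or fewer | 5.2% |

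Power for 70% against 40% (normal approximation without continuity correction):

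- At 48/48: Φ[(0.30·√48 − 1.379)/0.671] = Φ(1.043) = 85.1%.
- At 38/58: 83.5%.
- Averaged over all splits: 84.8%.

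Unrounded, the average loss is 85.15 − 84.78 = 0.37, or about 0.4 percentage points. Arm-size imbalance is of almost no consequence.

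**3. Imbalance in aetiology.** The article gives no shares, so a range is assumed. Arm size is Binomial(96, 0.5), and the number with a given cause in each arm is binomial with share p. Exact enumeration gives the probability that the two arms' shares differ by the stated amount:

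| Assumed share p | 10 points or more | 15 points or more |
|---|---|---|
| 10% | 10% | 2% |
| 20% | 22% | 7% |
| 30% | 29% | 11% |
| 40% | 32% | 14% |
| 50% | 34% | 14% |

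Hand check at p = 0.40: the standard deviation of the difference is √(4·0.40·0.60/96) = 0.10. Ten points is one standard deviation, with a two-sided normal tail of 32%. Holding the total number with the cause fixed moves these figures by at most about two points.

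**4. What such an imbalance could do.** The shift in the observed treatment difference is roughly the imbalance times the gap in improvement rate between causes. For illustration, let that gap be 30 points, as large as the whole planned effect (70 − 40). A 10-point imbalance then shifts the difference by 0.10 × 30 = 3 points, and a 15-point imbalance by 0.15 × 30 = 4.5 points, in either direction with equal chance.

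**5. Within an aetiology.** With a simple draw, a subgroup splits 2:1 or worse with probability 34% for 10 patients, 17% for 19, 6% for 29 and 3% for 38. Small aetiologies are the most exposed. Permuted blocks of four within a stratum would hold the difference to two patients.

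**6. Timing.** Study design divides patients after diagnosis, with ERCP among the diagnostic methods. Randomisation places the draw at transfer to the endoscope room, before the procedure. Where the cause is settled only at ERCP, both cannot be true.

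**The case against.** This is a condensed article, and operator, log and block scheme are details that a full protocol commonly holds. A reader might infer that allocation is unconcealed, unblocked and seen by the person enrolling. The article says none of this, and silence does not establish it. Consent is also signed before the draw, and an on-demand number cannot be foreseen, so the enroller cannot know the next assignment when recruiting. The proposed blocks would be somewhat more predictable in an open-label trial than the method they replace. All of this stands. It limits the first part of the point to the lack of a stated safeguard against redrawing or overriding.

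A reader might also infer that missing 48/48 undermines the sample size. It does not: the article sets 48 as a minimum per arm, fixes no total, and the power loss is trivial.

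Nor does chance imbalance confound the trial in the sense of bias. The tests' error rate already allows for it, and comparisons within one aetiology remain validly randomised.

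The objection does not dispose of the whole point. The article positively describes a draw made at the time of transfer, which is a different procedure from opening the next item of a locked list. It also states the tests without adjustment, next to an aim that depends on aetiology.

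**Conclusion.** The point holds in a limited form and should be acted on. The stated procedure is an on-demand draw from a public page, with no stated protection against redrawing or overriding in an open-label trial. Neither it nor the stated tests use aetiology, although the effect by aetiology is the first specific aim.

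Under a simple draw of 96, a between-arm difference of 10 points or more in an aetiology's share has a probability of about 10–34%, and of 15 points or more about 2–14%. This rests on assumed shares of 10–50%, a 1:1 ratio and no blocking, none of which the article states. The cost is precision and a weaker answer on aetiology, without bias in the overall test. The documents do not show that allocation was or will be manipulated; they show only that no barrier to it is described.

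**What to change.** - **Allocation:** generate the sequence once, in advance, in permuted blocks of varying size, stratified by benign or malignant obstruction. Hold it in sequentially numbered, opaque, sealed envelopes, with an existing staff member who does not enrol patients.
- **Timing:** reconcile Study design with Randomisation, so that allocation follows the diagnosis and precedes the start of UDCA. Stratifying by final cause is possible only then.
- **Analysis:** analyse the primary outcome with aetiology as a stratum or covariate, for example by Cochran-Mantel-Haenszel or logistic regression.
- **If randomisation stays before ERCP:** keep the locked list, without the aetiology strata, and adjust for aetiology in the analysis only.

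The cost is small: one list and somewhat more than 96 envelopes, because stratum totals are not known in advance and each stratum needs spares. No extra staff are needed. Moving the moment of randomisation is a real change to the procedure and must be written in. Blocks bring some predictability in an open-label trial, which varying their size limits.

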### Ethics

This study will be conducted in accordance with the principles of the Declaration of Helsinki. The study protocol has been approved by Ethics and Professional Committee at University Clinical Centre of Kosovo. Informed consent will be obtained from all participants.

### Data collection and statistical analyses

Data including serum-test results will be collected in a computer secured study platform. These data will be collected continuously, for each patient, starting one day before endoscopic procedure until the last data fourteen days after intervention.

X^2^-analysis or Fisher exact test will perform to test the differences in proportions of qualitative variables between groups. Mann Whitney U test and Kruskal Wallis test will use for testing the difference between quantitative variables when distribution is not normal and Student t-test or ANOVA test when distribution is normal. The level P < 0.05 will consider as the cut-off value for significance.

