### Hypothesis

The hypothesis of this trial is that patients with obstructive jaundice, in which will be administered UDCA, in the early phase after endoscopic intervention will have better and faster functional restoration of the liver than patients in the control group.

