### Outcomes

The primary outcome measure in this trial is liver functional restoration. The secondary outcome is assessment liver functional parameters in which, treatment with UDCA, will have greater impact. Follow-up measures will be collected one day prior endoscopic intervention, and on the third, fifth, seventh, tenth, twelfth and fourteenth days after endoscopic intervention.

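### Liver markers measured once before and six times after the procedure are to be compared by unadjusted tests chosen by observed normality, with no baseline adjustment, no use of the within-patient course and no measure of speed specified

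*Protocol article*

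**What the plan says.** All references are to the Protocol article.

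- **Data collection and statistical analyses** names the tests. Proportions are compared by chi-square or Fisher's exact test. For laboratory values, "Mann Whitney U test and Kruskal Wallis test will use for testing the difference between quantitative variables when distribution is not normal"; Student's t-test or ANOVA is used when the distribution is normal. Significance is P < 0.05. ANOVA appears as the parametric partner of Kruskal-Wallis, so it reads as one-way ANOVA rather than analysis of covariance or a repeated-measures analysis.
- **Outcomes** gives the schedule: "Follow-up measures will be collected one day prior endoscopic intervention, and on the third, fifth, seventh, tenth, twelfth and fourteenth days after endoscopic intervention". Study design repeats it for bilirubin, ALT, AST, GGT, alkaline phosphatase, albumin and cholesterol.
- **Hypothesis** states that treated patients "will have better and faster functional restoration of the liver than patients in the control group".
- **Inclusion criteria** set a lower limit for serum bilirubin (above 50 μmol/l) and no upper limit.
- **Power of the study** works from a binary outcome, "an improvement of 70% of liver functional tests in test group, and an improvement only 40% in control group", and concludes that "each of the two groups should have at least 48 patients".

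**The concern.** The design collects seven values per patient for every marker, but the listed methods are those for one independent value per patient. There are three consequences.

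1. **Precision.** With no upper bilirubin limit, starting values may differ a good deal between patients. If the starting value predicts the later one, an unadjusted comparison leaves that variation in the error term, although the trial has already measured it.
2. **Alignment with the hypothesis.** Half of the claim concerns speed. A comparison of levels at a given visit addresses the other half. The article defines no rate, slope or time-to-restoration variable, and names no treatment-by-time or time-to-event analysis.
3. **Choice of test by observed normality.** The method, and with it the quantity being compared (a difference in means or a shift in ranks), may change from marker to marker and from visit to visit according to the data. Results would then be hard to set side by side, and one specific aim is to compare the effect across markers.

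**Working it through.** **Inputs.** From the article: 48 per arm; alpha 0.05 (two-sided assumed, since sidedness is not stated); power 80%; one pre-procedure and six follow-up values. Assumed, because the article gives no figure: the correlation r between a marker's pre-procedure and follow-up values, taken as 0.3, 0.5 and 0.7.

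**Step 1: the plan's own figure.** For 70% against 40%, the pooled normal formula is

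n = [1.960·√(2·0.55·0.45) + 0.842·√(0.7·0.3 + 0.4·0.6)]² / 0.30² = 42 per arm,

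or 49 with continuity correction. Fisher's exact test with 48 per arm has 80.0% power. The stated 48 therefore reproduces, and the sample size is not in question. It rests on a difference in proportions, however, so the steps below concern only the quantitative comparisons of markers.

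**Step 2: variance.** With the follow-up SD set to 1, the variance per patient is:

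- raw follow-up value: 1
- change from baseline (equal SDs before and after assumed): 2(1 − r)
- follow-up value adjusted for baseline: 1 − r²

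The ratio of adjusted to raw is 1 − r². The ratio of adjusted to change is (1 − r²) / [2(1 − r)] = (1 + r)/2. The equivalent size per arm is 48 divided by the ratio.

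| r | Adjusted vs raw: ratio (cut) | 48 is worth | Adjusted vs change: ratio (cut) | 48 is worth |
|---|---|---|---|---|
| 0.3 | 0.91 (9%) | 48/0.91 = 52.7 | 0.65 (35%) | 48/0.65 = 73.8 |
| 0.5 | 0.75 (25%) | 48/0.75 = 64.0 | 0.75 (25%) | 48/0.75 = 64.0 |
| 0.7 | 0.51 (49%) | 48/0.51 = 94.1 | 0.85 (15%) | 48/0.85 = 56.5 |

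**Step 3: power.** With 48 per arm, an unadjusted comparison of raw values at one visit has 80% power for a difference of √(2/48)·(1.960 + 0.842) = 0.572 SD. For that same difference, power = Φ(2.802/√v − 1.960), where v is the variance from step 2.

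| r | Raw follow-up | Change from baseline | Baseline-adjusted |
|---|---|---|---|
| 0.3 | 80.0% | 65.8% | 83.6% |
| 0.5 | 80.0% | 80.0% | 89.9% |
| 0.7 | 80.0% | 95.1% | 97.5% |

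Adjustment is best in every row. Change from baseline beats the raw value only when r exceeds 0.5.

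**Step 4: speed.** Set against the hypothesis, none of the named tests compares the course of recovery when applied to visit values. Applied to a derived time to restoration, a rank test could do so, but no such variable is defined. Such a variable would also be cut off at day 14, while the Background cites at least four to six weeks for the liver's main functions to return to normal. If restoration means a normal value, many patients may not reach it within follow-up, and none of the named tests is designed for censored times.

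**The case against.** - **The analysed variable is not named.** The tests are listed for quantitative variables in general, and the power section speaks of improvement, which implies some reference to the starting value. A reader might infer that the plan ignores the pre-procedure value. The text does not establish that; it supports only that no adjustment is specified. This stands, and it is why both comparators are shown above. Adjustment is better than either.
- **Speed is not out of reach of these tests.** A reader might infer that the listed methods cannot test it. A rank test on a slope or a time, or a comparison of proportions improved at an early visit, would address it, crudely or with difficulty over censoring. The gap is that no speed variable or analysis is specified.
- **ANOVA or Kruskal-Wallis across visits would break the independence assumption.** Nothing in the article says they will be used that way. The specific aim on aetiology, with several causes of jaundice, is a natural use for tests of more than two groups. This is not counted against the plan.
- **Validity.** Unadjusted comparisons of randomised arms are valid, and chance baseline imbalance is already covered by the error rate. A reader might infer bias; the documents do not support that.
- **Detail left to an analysis plan.** Covariance structure and covariate lists commonly are. But the article does not leave the method open: it names the tests and the rule for choosing between them.
- **The wide spread of starting values** is inferred from the missing upper bilirubin limit. No spread is given.

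**Conclusion.** The point holds as a matter of efficiency and alignment. The article commits to unadjusted tests, chosen by observed normality, for serial markers. It specifies no baseline adjustment, no use of the within-patient course and no analysis matched to the speed half of its hypothesis.

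The loss depends on r, which is assumed, and on which variable would otherwise be analysed, which is not stated. Over r from 0.3 to 0.7 the variance saving is 9% to 49% against raw follow-up values and 35% down to 15% against change from baseline. The largest equivalent, 94 per arm, belongs only to raw values at r = 0.7; against change from baseline at the same r it is about 56. The change-from-baseline figures also assume equal SDs before and after the procedure. Neither set describes the 70% against 40% comparison that produced 48 per arm.

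This should be changed, but the trial's validity does not depend on it.

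**What to change.** - **Serial markers.** Replace the unadjusted tests with a repeated-measures model for each marker, with the pre-procedure value as covariate and terms for treatment, visit and treatment-by-visit. Fix the scale in advance (log where a marker is expected to be skewed) rather than after looking at the data. Name one primary contrast.
- **Speed.** Pre-specify one analysis: either a treatment-by-visit contrast, or time to a defined restoration threshold with censoring at day 14. The investigators would have to define the threshold.
- **Responder analysis.** If a proportion improved is analysed, adjust it for baseline bilirubin.
- **Sensitivity.** Keep the rank test as a sensitivity analysis.

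The cost is slightly more analysis work and no new measurements. An unstructured covariance over six visits has 6·7/2 = 21 parameters, to be estimated from about 96 patients (2 × 48), so a simpler structure should be named in advance as the fallback if the model does not converge.
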